## 5.6 Sample size calculation

Primary psychological outcome: Depression

In our previous study, 24 MADRS scores in women randomized to NET-EN were 8.3 (standard deviation 7.5). Based on this standard deviation, to show a difference of 2 between the study groups with 95% certainty and 80% power would require 221 participants per group, and allowing for 15% loss to follow-up, 260 per group. (<http://pharmaschool.co/size4.asp>).

Primary biological outcome: serum 17 $\beta$  estradiol

In our previous study, 17 $\beta$  estradiol levels in women randomized to NET-EN were 136 pmol/L (standard deviation 119). Based on this standard deviation, to show a difference of 35 pmol/L in either direction between groups with 95% certainty and 80% power would require 181 participants per group, and allowing for 15% loss to follow-up, 213 per group (<http://pharmaschool.co/size4.asp>).

Because of multiple outcomes to be measured, the remaining outcome comparisons will be regarded as exploratory. In general, studies of biomarkers such as immune effects have used considerably smaller sample sizes.

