#### **5.9 Criteria for discontinuation of a participant**

Participants who decline to remain in the study will be discontinued. Stopping or changing the allocated method will not be a reason for discontinuation, as analysis will be by intention to treat. Pregnancy or HIV sero-conversion will not be a reason for discontinuation, as other outcomes will remain relevant.

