### **8.2 Data analysis plan**

Analysis will be by intention to treat, and the results will be reported according to the CONSORT guidelines. Baseline characteristics will be compared to confirm the effectiveness of the

randomization process. Numbers and baseline characteristics of losses to follow-up will be compared between groups to detect any imbalances in loss to follow-up. Number of subjects, number of missing values and percentages will be reported for categorical variables. Number of subjects, number of missing values, minima, maxima, means and standard deviations will be reported for continuous variables. Appropriate transformation of non-normal or skewed measurement will be performed on continuous variables. If transformations do not generate a distribution approaching normality, medians and IQR will be reported.

For incidence outcomes (eg pregnancy and HIV seroconversion) with varying duration of follow up between groups, data will be adjusted for duration of follow up.

Categorical variables will be compared as risk ratios with 95% confidence intervals. For continuous data, mean differences with 95% confidence intervals will be reported.

The primary analysis will be based on all subjects with outcome data available. A sensitivity analysis will be performed that only analyzes participants who have neither discontinued nor switched contraceptive methods to assess the impact of switching and discontinuation.

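### The primary analysis is fixed as available-case under an unqualified ITT label, leaving only a descriptive comparison of losses as a check on informative dropout for BDI-II

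*Protocol*

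**What the plan says.** Protocol Section 8.2 opens with the label: "Analysis will be by intention to treat, and the results will be reported according to the CONSORT guidelines". Later in the same section it defines who enters the main comparison: "The primary analysis will be based on all subjects with outcome data available". Continuous outcomes are to be reported as mean differences with 95% confidence intervals.

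Two further statements in Section 8.2 bear on loss and non-adherence:
- A sensitivity analysis: "A sensitivity analysis will be performed that only analyzes participants who have neither discontinued nor switched contraceptive methods".
- A description of losses: "Numbers and baseline characteristics of losses to follow-up will be compared between groups to detect any imbalances in loss to follow-up". Counts of missing values are also to be reported.

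Section 5.9 keeps women in the trial whatever happens to their method: "Stopping or changing the allocated method will not be a reason for discontinuation, as analysis will be by intention to treat".

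Section 5.6 deals with loss through the sample size. For the depression outcome it says "to show a difference of 2 between the study groups with 95% certainty and 80% power would require 221 participants per group", and then "allowing for 15% loss to follow-up, 260 per group". Section 4.1 makes BDI-II one of the two primary outcomes. BDI-II is scheduled at enrolment (Table 1) and six-monthly afterwards (Table 2).

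**The concern.** How missing outcomes enter the primary analysis is a stated choice here, not a matter left open for the SAP. A SAP could add analyses, but it could not change the primary one without departing from this sentence.

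An available-case mean difference estimates the effect in all randomised women only if the losses have the same net influence on the mean in both arms. The protocol does not state that assumption. The sensitivity analysis it names does not probe it: restricting to women who stayed on their method selects further on behaviour after randomisation and brings back no woman whose outcome is missing.

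A woman lost before month 6 has a baseline BDI-II but no follow-up score, so she drops out of the comparison. Enlarging the sample for loss restores precision but does nothing about bias. At stake is how far a BDI-II result can be trusted when the target difference is only 2 points.

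**Working it through.** **Inputs**
- SD 7.5, target difference 2, 80% power, 221 evaluable and 260 enrolled per group, 15% loss: Section 5.6. The SD comes from MADRS scores in an earlier trial and is applied to BDI-II.
- Two-sided 5% test: my reading of 95% certainty in Section 5.6.
- Month 6 as the BDI-II time point: taken from the visit schedule in Table 2.
- d, the mean of missing minus the mean of observed women within an arm: not in the protocol, so assumed and shown over a range.

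**Step 1. Reproduce the plan's figures.** n per group = 2 × (1.96 + 0.8416)² × 7.5² / 2² = 220.8, so 221. Then 221 / 0.85 = 260. Both agree with Section 5.6. Conversely, 260 × 0.15 = 39 women missing per arm.

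**Step 2. Standard error.** 7.5 × √(2/221) = 0.713. The 95% half-width is 1.96 × 0.713 = 1.40.

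**Step 3. Bias.** With a share m missing in an arm, the mean in all randomised women is the observed mean plus m × d. The full-cohort difference minus the available-case difference is therefore m₁d₁ − m₂d₂.

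Take m = 0.15 in both arms, d in one arm and zero in the other, so that the bias is b = 0.15 × d:

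| d (points) | Bias b | Share of 2-point target | Type I error | Power at true difference 2, bias toward null |
|---|---|---|---|---|
| 3 | 0.45 | 23% | 10% | 58% |
| 5 | 0.75 | 38% | 18% | 42% |
| 7.5 | 1.13 | 56% | 35% | 23% |

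Type I error is P(|Z + b/0.713| > 1.96). Power is P(Z > 1.96 − (2 − b)/0.713); with b = 0 it is 80%.

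**Step 4. When the bias cancels.** With 15% missing in each arm and the same d in both, 0.15d − 0.15d = 0. If the shares differ, say 10% and 20%, an equal gap no longer cancels. With d = 7.5 in both arms, the result is 0.10 × 7.5 − 0.20 × 7.5 = −0.75.

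**Step 5. Tipping values for an observed difference of 2.** At 15% missing per arm, a one-arm gap of (2 − 1.40)/0.15, about 4.0 points, takes the interval to zero. A gap of 2/0.15 = 13.3 points removes the difference altogether. These values use the available-case standard error and ignore the extra uncertainty from imputation.

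**The case against.** The case on the other side is substantial, and several parts of it stand.

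- **The plan does look at losses.** A reader might infer that nothing in it would reveal a problem. That goes too far: Section 8.2 compares the numbers and baseline profile of losses by arm, and baseline BDI-II is available for this. What the comparison cannot do is show dependence on the month-6 score of women who were not seen, or correct the estimate.
- **Stopping the method is not leaving the study.** A reader might infer from Section 1, which reports high discontinuation of injectables, that women will leave the trial because of side effects. Those figures concern method use. Section 5.9 keeps such women in follow-up, and Sections 5.8.5 and 9 plan calls, alternative contacts and home visits. Side-effect-driven loss is not shown. Equal loss cannot be presumed either, since injection visits are two-monthly in one arm and three-monthly in the other.
- **The ITT label is not a contradiction.** Analysing women as randomised where outcomes exist is common usage, and Section 5.9 uses the term in that sense. The fault is the missing qualification and the unstated assumption.
- **The 15% is a planning allowance**, not a forecast, and no figure in the protocol supports any value of d. Placing the whole gap in one arm is an unfavourable case. Both arms receive progestogen-only injectables, and similar loss would cancel.
- **The SAP is not shown.** It may contain a missing-data sensitivity analysis, and its absence from the protocol does not prove that none is planned. This does not alter the primary-analysis sentence.

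**Conclusion.** The point holds in a limited form. Section 8.2 commits the trial to an available-case mean difference under an unqualified ITT label. The only sensitivity analysis it names is about adherence to the method, so within the protocol the defence against informative loss is descriptive.

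The possible bias in the BDI-II difference is 0.15 times the between-arm difference in the missing-versus-observed gap. For one-arm gaps of 3 to 7.5 points that is 0.45 to 1.13 points, or 23% to 56% of the target. This rests on 15% missing in each arm, an SD of 7.5 carried over from MADRS, and gaps that are assumptions throughout. The result shows vulnerability. It does not show that bias will occur, and reversing a 2-point finding entirely would take an extreme gap of about 13 points. The change is worth making because BDI-II is a primary outcome and the remedy is cheap.

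**What to change.** Reword Section 8.2 as follows:
1. State that women are analysed in the arm to which they were randomised, and state the assumption made about missing outcomes.
2. Estimate the month-6 BDI-II difference conditional on baseline BDI-II and site. Use either a baseline-adjusted model or multiple imputation by arm from data scheduled before loss: baseline BDI-II, site, age and recorded injection dates. The reason for stopping the method should not be a predictor, because Section 5.8.5 schedules no follow-up record of it before month 6.
3. Add a delta-adjusted tipping-point sensitivity analysis that shifts imputed BDI-II separately in each arm over a stated range, for example 0 to 7.5 points (one planning SD).
4. Keep the unadjusted available-case difference as a supportive result, and keep the descriptive comparison of losses.

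A repeated-measures model for estradiol is optional. Its only post-baseline samples are at month 6 and seven days later, so it adds no post-baseline information for women lost before month 6.

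The cost is wording, some programming and an explicit statement of the model and imputation assumptions. No additional visits, samples or participants are needed. Conditioning on baseline deals only with loss that baseline data explain; the tipping-point analysis is there for the rest.

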### **8.3 Study timeline**

Ethical approval of protocol: 2 months

Development of the manual of procedures: 1 month

Administrative and organizational arrangements at sites: 1 month

Training for research staff: 1 month

Recruitment: 4 months

Follow-up: 7 months, pending funding 12-18 months

Data cleaning and analysis and manuscript: 3 months

### **9. Main problems anticipated and proposed solutions**

Loss to follow-up. Telephone calls will be used to remind participants of appointments. Mobile phone ownership is very high in our setting. We will confirm telephone numbers at each contact as well as numbers of friends or family whom participants give permission for the research team to contact. Home visits will be used if telephone contact fails, subject to specific consent for home visits having been given. If women are unable to come to the final visit in person, study personnel will go to their home or another place of their choosing, such as their local clinic, provided they have given consent for such visits.

Finally, contraceptive switching and method discontinuation may make it difficult to interpret our data. In order to minimize the impact of this, providers will carefully counsel women about side effects to expect and how to manage them.

## **10. Applicability of results**

The rationale for this study, and the need for a more definitive answer, has been explained above. The results of this study will respond to an urgent need for better information for women and policy-makers, and will be relevant to settings similar to that of the study sites.

## **11. Ethical considerations:**

Ethical approval will be obtained before data collection began from the Faculty of Health Sciences Human Research Ethics Committee (FHS HREC) of the University of Watwatersrand and University of Cape Town, and from the East London Hospital institutional Ethics Committee. Permission to conduct the study will be requested from the Provincial Departments of Health (state which: KZN, EC I guess WC not needed?). The South African Health Products Regulatory Authority (SAHPRA) will be notified of the study.

This study adheres to the ethical principles outlined in the Declaration of Helsinki and the Constitution of the Republic of South Africa (Bill of Rights) (Devenish, 1999).

### **12.1. Study population, recruitment strategy and informed consent process**

The inclusion criteria have been made as inclusive as possible so that a minimum number of women are excluded from the opportunity of participating in the study (see section 5.4). Research staff with GCP certification and specific training in the recruitment procedures will conduct recruitment (5.8.1). Informed consent will comply with requirements for research on human subjects.

### **12.2 Perceived risks and benefits of the study, both at the individual and community levels**

Benefits of the study

- The study will provide sound evidence for guiding the choice of family planning methods by women in the future
- High-profile community information as part of the study will stimulate community awareness of family planning, and increase contraception uptake, leading to an overall reduction in unplanned pregnancies, pregnancy termination requests, and complications of unplanned pregnancies.
- Participants will receive high quality, respectful contraceptive care from study staff in accordance with routine health service procedures.

### Risks of the study

Both methods of family planning have risks and benefits, but these are related to the participants' need for family planning, not to the research. It is not known whether one method is overall better or safer than the other. The World Health Organization recommends both methods for widespread use, and does not distinguish between their medical eligibility criteria. The discomforts of the trial procedures are completing the questionnaires and the blood and genital tract sampling. Genital tract sampling will be non-invasive, by means of cytobrush sampling from the cervix and swabs from the vaginal walls. Six-monthly HIV tests are recommended as part of the national health strategy. Knowledge of HIV results will be of benefit to participants in terms of reassurance or advice to seek appropriate care.

Adverse events will be managed according to the 'Good clinical Practice' guidelines: Any untoward occurrence will be reported as an adverse event. Any adverse event resulting in death, a life-threatening condition, hospitalisation or prolongation of hospital stay, persistent or significant disability/incapacity, or congenital anomaly, will be reported as a serious adverse event within 2 working days. Serious adverse events will be reported to the data monitoring and safety committee, who will be independent of the trial, and the relevant ethics committees.

### **12.3 Safeguards to protect any recognized vulnerability of the study participants**

Women seeking contraceptive services may be vulnerable to coercion, especially those seeking services after a pregnancy termination. Only women who, after routine counselling in the regular services, desire a contraceptive method, and request injectable contraception, will be approached for enrolment. As detailed above (section 2.5.7), women who choose not to enrol will nonetheless be offered the contraceptive method of their choice.

### **12.4 Reimbursement or compensation to study participants**

Participants will be reimbursed R250 for their time and transportation costs for in-person visits, and R100 for contraception only visits.

### **12.5 Access to treatment or counselling for conditions either identified during screening of potential participants or resulting from the study intervention**

Please see sections 5.4.2 , 5.7 and 5.8.1 for details on referral processes for women who are diagnosed with HIV, pregnancy, or any other medical condition requiring treatment in the context of the study.

## **12.6 Responsiveness of the project to community needs and priorities**

Recruitment for the ECHO study has revealed a high level of acceptance of participation among all stakeholders. Both sites have active Community Advisory Boards who have approved the study at the planning stage, and will continue to give input during the study.

## **12.7 Deception**

Deception will not be employed in this study.

## **13. Gender considerations**

### **13.1 Describe how women and men are affected by the public health need that the study addresses, and whether this is a need expressed or felt by women and/or men**

Maternal deaths account for about 400 000 deaths annually, most of which take place in low-income countries. Improved information on and understanding of contraception choices will promote family planning and reduce unintended pregnancies. This research is directly related to attempts to reduce maternal mortality, as well as to identify strategies to mitigate HIV risk.

### **13.2 Explain how the research contributes to identifying and/or reducing inequities between women and men in sexual and reproductive health and health care.**

The study will provide improved information on two confidential, woman-controlled methods for contraception. Empowering women to make their own decisions about reproduction is seen as central to promoting gender equity.

### **13.3 Describe measures taken to facilitate the individual participation of women or men in the research process in light of their different life situations**

This project will recruit women only, and addresses gender equity by empowering women to access confidential contraception.

### **13.4 Describe measures taken to ensure that community involvement is inclusive**

Community communication strategies will include posters informing the community at large of the study, with contact numbers for input or queries, and when possible, research staff will be interviewed on local radio, and give talks at community forums such as churches. The sites' community advisory boards will play an active part in the study planning and implementation. The great majority of researchers at all the proposed sites are female, from local communities.

## **14. Environmental impact of the project**

As this study takes place within the context of the regular health services, the additional environmental impact is minimal. Additionally, the provision of voluntary contraceptive services may have a positive environmental impact by reducing the rate of unintended pregnancies.

## **15. Plans for dissemination and use of project results**

Trial participants will be asked whether they wish to receive a brief report on the results of the study, and how.

The results will be important for health workers counselling women on their family planning choices, and will be made available to the Department of Health to inform family planning policy and training. Apart from primary publication in a peer-reviewed journal, the data will be incorporated into our Cochrane reviews on hormonal contraception, in the Cochrane Library, recognised as a leading source of evidence-based information.

## **16. Budget**

### **Annual budget:**

Injectables will be provided by routine health services as per letter from the Deputy Director-General, Dept of Health

Data management, statistical analysis and trial monitoring will be covered by the SA MRC.

Certain laboratory studies and sample archiving will be covered by Department of Molecular and Cell Biology, University of Cape Town ([name])

Remaining budget (Trial staff, management, supplies, sample transport, laboratory tests, participant costs, etc.): 2017/18 financial year: **R4 967 770** and 2018/19 financial year: **R4 967 77.**

**Total Budget : R 9 935 540**

## Appendix 1: 28 Days Daily Diary

| Identification                                                           |  | WHICH INJECTION STUDY (PART 1)                                                                                                                                                                                                                                                                                                                                                                        |  |  |  |  |  |  |  |  |  |  |  |  |  |  |  |  |  |  |  |  |  |  |
|--------------------------------------------------------------------------|--|-------------------------------------------------------------------------------------------------------------------------------------------------------------------------------------------------------------------------------------------------------------------------------------------------------------------------------------------------------------------------------------------------------|--|--|--|--|--|--|--|--|--|--|--|--|--|--|--|--|--|--|--|--|--|--|
| Subject number                                                           |  | Start date                                                                                                                                                                                                                                                                                                                                                                                            |  |  |  |  |  |  |  |  |  |  |  |  |  |  |  |  |  |  |  |  |  |  |
| Date of birth                                                            |  | End date                                                                                                                                                                                                                                                                                                                                                                                              |  |  |  |  |  |  |  |  |  |  |  |  |  |  |  |  |  |  |  |  |  |  |
| Please tell us what happened from mid-day yesterday until mid-day today? |  |                                                                                                                                                                                                                                                                                                                                                                                                       |  |  |  |  |  |  |  |  |  |  |  |  |  |  |  |  |  |  |  |  |  |  |
|                                                                          |  | 
 12345678910111213141516171819202122 
 |  |  |  |  |  |  |  |  |  |  |  |  |  |  |  |  |  |  |  |  |  |  |
| 1 Have you been menstruating?                                            |  |                                                                                                                                                                                                                                                                                                                                                                                                       |  |  |  |  |  |  |  |  |  |  |  |  |  |  |  |  |  |  |  |  |  |  |
| 0=No      2.Light                                                        |  |                                                                                                                                                                                                                                                                                                                                                                                                       |  |  |  |  |  |  |  |  |  |  |  |  |  |  |  |  |  |  |  |  |  |  |
| 1.Normal    3.Heavy                                                      |  |                                                                                                                                                                                                                                                                                                                                                                                                       |  |  |  |  |  |  |  |  |  |  |  |  |  |  |  |  |  |  |  |  |  |  |
| 2 Has your menstruation been?                                            |  |                                                                                                                                                                                                                                                                                                                                                                                                       |  |  |  |  |  |  |  |  |  |  |  |  |  |  |  |  |  |  |  |  |  |  |
| 0.No menstruation    2.Mild pain                                         |  |                                                                                                                                                                                                                                                                                                                                                                                                       |  |  |  |  |  |  |  |  |  |  |  |  |  |  |  |  |  |  |  |  |  |  |
| 1.Painless menstruation 3.Severe pain                                    |  |                                                                                                                                                                                                                                                                                                                                                                                                       |  |  |  |  |  |  |  |  |  |  |  |  |  |  |  |  |  |  |  |  |  |  |
| 3 Have you had sexual intercourse?                                       |  |                                                                                                                                                                                                                                                                                                                                                                                                       |  |  |  |  |  |  |  |  |  |  |  |  |  |  |  |  |  |  |  |  |  |  |
| 0.No intercourse if yes 2.Casual partner                                 |  |                                                                                                                                                                                                                                                                                                                                                                                                       |  |  |  |  |  |  |  |  |  |  |  |  |  |  |  |  |  |  |  |  |  |  |
| 1.Steady partner only                                                    |  |                                                                                                                                                                                                                                                                                                                                                                                                       |  |  |  |  |  |  |  |  |  |  |  |  |  |  |  |  |  |  |  |  |  |  |
| 4 If yes Q4 sexual intercourse? Was condom used?                         |  |                                                                                                                                                                                                                                                                                                                                                                                                       |  |  |  |  |  |  |  |  |  |  |  |  |  |  |  |  |  |  |  |  |  |  |
| 0.No intercourse      2.No condom                                        |  |                                                                                                                                                                                                                                                                                                                                                                                                       |  |  |  |  |  |  |  |  |  |  |  |  |  |  |  |  |  |  |  |  |  |  |
| 1.Yes condom                                                             |  |                                                                                                                                                                                                                                                                                                                                                                                                       |  |  |  |  |  |  |  |  |  |  |  |  |  |  |  |  |  |  |  |  |  |  |
| 5 Have you felt sad for no real reason ?                                 |  |                                                                                                                                                                                                                                                                                                                                                                                                       |  |  |  |  |  |  |  |  |  |  |  |  |  |  |  |  |  |  |  |  |  |  |
| 0 = No                                                                   |  |                                                                                                                                                                                                                                                                                                                                                                                                       |  |  |  |  |  |  |  |  |  |  |  |  |  |  |  |  |  |  |  |  |  |  |
| 1 = Yes                                                                  |  |                                                                                                                                                                                                                                                                                                                                                                                                       |  |  |  |  |  |  |  |  |  |  |  |  |  |  |  |  |  |  |  |  |  |  |
| 6 Have you felt an urge to have sexual intercourse?                      |  |                                                                                                                                                                                                                                                                                                                                                                                                       |  |  |  |  |  |  |  |  |  |  |  |  |  |  |  |  |  |  |  |  |  |  |
| 0 = No                                                                   |  |                                                                                                                                                                                                                                                                                                                                                                                                       |  |  |  |  |  |  |  |  |  |  |  |  |  |  |  |  |  |  |  |  |  |  |
| 1 = Yes                                                                  |  |                                                                                                                                                                                                                                                                                                                                                                                                       |  |  |  |  |  |  |  |  |  |  |  |  |  |  |  |  |  |  |  |  |  |  |
| 7 Did you feel that your partner loves you?                              |  |                                                                                                                                                                                                                                                                                                                                                                                                       |  |  |  |  |  |  |  |  |  |  |  |  |  |  |  |  |  |  |  |  |  |  |
| 0.No      2 = No partner                                                 |  |                                                                                                                                                                                                                                                                                                                                                                                                       |  |  |  |  |  |  |  |  |  |  |  |  |  |  |  |  |  |  |  |  |  |  |
| 1. Yes                                                                   |  |                                                                                                                                                                                                                                                                                                                                                                                                       |  |  |  |  |  |  |  |  |  |  |  |  |  |  |  |  |  |  |  |  |  |  |

Daily Diary

